# Ultrasound in managing extrapulmonary tuberculosis: a randomized controlled two-center study

**DOI:** 10.1186/s12879-020-05073-9

**Published:** 2020-05-15

**Keywords:** Sonography, FASH, Extrapulmonary, Tuberculosis, Sub-Saharan Africa

## Abstract

**Background:**

Patients with clinically suspected tuberculosis are often treated empirically, as diagnosis - especially of extrapulmonary tuberculosis - remains challenging. This leads to an overtreatment of tuberculosis and to underdiagnosis of possible differential diagnoses.

**Methods:**

This open-label, parallel-group, superiority randomized controlled trial is done in a rural and an urban center in Tanzania. HIV-positive and -negative adults (≥18 years) with clinically suspected extrapulmonary tuberculosis are randomized in a 1:1 ratio to an intervention- or control group, stratified by center and HIV status. The intervention consists of a management algorithm including extended focused assessment of sonography for HIV and tuberculosis (eFASH) in combination with chest X-ray and microbiological tests. Treatment with anti-tuberculosis drugs is started, if eFASH is positive, chest X-ray suggests tuberculosis, or a microbiological result is positive for tuberculosis. Patients in the control group are managed according national guidelines. Treatment is started if microbiology is positive or empirically according to the treating physician. The primary outcome is the proportion of correctly managed patients at 6 months (i.e patients who were treated with anti-tuberculosis treatment and had definite or probable tuberculosis, and patients who were not treated with anti-tuberculosis treatment and did not have tuberculosis). Secondary outcomes are the proportion of symptom-free patients at two and 6 months, and time to death. The sample size is 650 patients.

**Discussion:**

This study will determine, whether ultrasound in combination with other tests can increase the proportion of correctly managed patients with clinically suspected extrapulmonary tuberculosis, thus reducing overtreatment with anti-tuberculosis drugs.

## Background

In resource-limited settings with a high tuberculosis prevalence, almost half of patients are treated empirically with anti-tuberculosis drugs upon clinical suspicion only [1–3]. Besides lack of available tests, this is mainly due to the poor sensitivity of microbiological tests, especially in patients co-infected with human immunodeficiency virus (HIV) or in those with suspected extrapulmonary tuberculosis [4, 5]. The decision to treat tuberculosis based on clinical signs and symptoms only has a low accuracy for culture-confirmed tuberculosis, and 30–60% of these decisions lead to false treatment [1, 3, 6]. The consequence is, that patients are unnecessarily exposed to potentially toxic drugs for long time periods, and the diagnosis of their real disease such as other infections, cancer or heart failure is delayed, or missed. Additional diagnostic methods are therefore needed to distinguish tuberculosis from other diseases with similar symptoms.

Ultrasound is a widely available diagnostic tool, which is used in various medical fields. Focused Assessment with Sonography for HIV and Tuberculosis (FASH) is a useful tool to detect signs of extrapulmonary tuberculosis, namely pleural and pericardial effusion, enlarged abdominal lymph nodes, hypoechogenic lesions in the spleen and the liver, ascites and thickening of the bowel wall [7]. FASH can be performed as a point of care bedside test and can be taught to personnel with little or no previous experience in ultrasonography [8]. In our observational study from rural Tanzania including 191 HIV-positive and -negative patients with suspected pulmonary or extrapulmonary tuberculosis, abnormal chest X-ray, presence of ≥1 FASH-sign, and elevated body temperature were independently associated with confirmed tuberculosis. A combination of ≥1 FASH sign, abnormal chest X-ray, and temperature ≥ 37.5 °C had a high (99.1%) sensitivity but a low (35.2%) specificity for confirmed tuberculosis. We concluded that ultrasound might be useful to exclude tuberculosis, in combination with other tests [9]. In a recent Cochrane metanalysis including HIV-positive adults, FASH signs predicted tuberculosis with a moderate diagnostic performance only. The authors also concluded that ultrasound results should be considered in combination with other tests, such as chest X-ray and Xpert MTB/RIF® only [10]. No randomized controlled trial evaluating sonography for the diagnosis of tuberculosis has been done yet.

With our randomized controlled trial, we aim to determine whether sonography, added to chest X-ray and microbiological tests, has an impact on the proportion of correctly managed patients with suspected extrapulmonary tuberculosis, and on morbidity and mortality. We have added the sonography of axillary and cervical lymph nodes, of the chest, and of the vena cava to the FASH protocol, and call it extended FASH (eFASH). We hypothesize that the proportion of correctly managed patients after 6 months will be higher in the intervention group versus the control group.

## Methods

### Study design and setting

This is a two-center, open-label, parallel-group, superiority randomized controlled trial. Patients are consecutively recruited at St. Francis Referral Hospital, Ifakara and Mwananyamala Regional Referral Hospital, Dar es Salaam, United Republic of Tanzania.

St. Francis Referral Hospital serves a rural population of about 1 million people as a referral center. It includes the Chronic Diseases Clinic of Ifakara (CDCI), which cares for over 4000 people living with HIV [11, 12] and/or tuberculosis [13]. Mwananyamala Regional Referral Hospital serves an urban population of Dar es Salaam and is a referral center for tuberculosis within the Kinondoni district. The planned study period is 2 years, including 6 months of follow-up.

### Patients

All HIV-positive and -negative adults aged ≥18 years presenting to any department of the St. Francis Referral Hospital, CDCI or Mwananyamala Regional Referral Hospital are screened by trained study personnel. Eligible patients are those fulfilling clinical screening criteria for extrapulmonary tuberculosis, with or without concomitant signs of pulmonary tuberculosis (Table 1).

**Table 1 Tab1:** **Eligibility criteria**

Inclusion criteria	- Adult (≥18 years) - Documented HIV status (HIV- positive and HIV- negative) - Suspected extrapulmonary tuberculosis*: presence of ≥1 sign or symptom of the following: • Fever of any duration, • Night sweat during 3 weeks within the last 4 weeks • Weight loss AND presence of ≥1 sign or symptom of the following: • Nuchal, cervical, axillary or generalized lymphadenopathy • Abdominal pain or ascites • Neurological symptoms (reduced consciousness, confusion, stiff neck, focal signs, persisting headache) • Presence of severe anaemia (hemoglobin < 8 g/dl) in an HIV infected patient under antiretroviral treatment • Local pain and spinal deformity, or arthritis suggesting spinal or osteoarticular tuberculosis • Painless hematuria or sterile pyuria, scrotal nodules or epididymal Hardening, or salpingitis suggesting urogenital tuberculosis • Chest x-ray with signs of miliary pattern, pleural effusion or suspected pericardial effusion AND No other obvious explanation for these signs ** with or without concomitant signs of pulmonary tuberculosis (i.e cough or chest x-ray with upper lobe infiltrate, cavernous lesion)*
Exclusion criteria	- Pregnancy
	- Patients already on anti-tuberculosis treatment
	- Refusal to participate or sign informed consent
	- Not available for follow-up visits

### Study procedures intervention group and control group

Before randomization, all eligible and consenting patients receive a clinical evaluation including an interview with a systematic assessment of symptoms. Physical examination including measuring body weight and height, blood pressure, heart rate, chest and abdominal examination, and palpation of lymph nodes is done by the study physician. All patients receive a chest X-ray, an HIV test if the HIV status is not documented and blood tests for hemoglobin, creatinine, and alanine aminotransferase. Microbiological analyses are performed as follows: If a patient can produce sputum, conventional Xpert MTB/RIF® (Cefeid, Sunnyvale, CA) is done. We decided to use the conventional Xpert in sputum because the Xpert MTB/RIF Ultra® assay has a lower specificity in sputum, and might generate false positive results [14]. Additionally, sputum samples are sent for solid culture after adding cetylpyridinium chloride and N-acetyl-l-cysteine-sodium hydroxide and are then inoculated on Löwenstein-Jensen medium [15]. For all patients, urine samples are collected and Xpert MTB/RIF Ultra® assay is used [16, 17].

Patients allocated to the intervention group receive additionally an eFASH examination. Anti-tuberculosis management and treatment is done according to an algorithm (see Fig. 1). Patients allocated to the control group are treated according national guidelines [18]. eFASH consists of sonographic evaluation of the following:
Original FASH signs: Pleural or pericardial effusion, hypoechogenic lesions in spleen and liver, abdominal lymphnodes > 1.5 cm, ascites, bowel wall thickeningExtended signs: Diameter of the vena cava in order to detect signs for heart failure; axillary, nuchal and cervical lymph nodes > 1.5 cm; and B-lines and echogenic bright granular artefacts in the subpleural area in chest sonography. This is done by multiple scans of the main bilateral chest areas (anterior superior, lateral, posterior superior, posterior inferior of the left and right chest) [19].

**Fig. 1 Fig1:**
[figure not shown]
Algorithm for management of intervention group and control group. LN: lymph node; TB: Tuberculosis; eFASH: Extended Focused Assessment with Sonography for HIV and Tuberculosis; PE: pericardial effusion. **†** anti-tuberculosis treatment is started in case of a positive microbiological result

eFASH is performed by two trained study doctors in patients in the intervention group only, before availability of microbiological results. All sonographical investigations are reviewed by an independent board-certified sonographer with a minimum experience of 5 years after the examination. This review will not influence the patient management, but it will be included in the final interpretation of the data. All sonographical examinations are done with a Sonobook 9 ultrasound machine (Chison, Jiangsu, China). In case of pleural fluid or ascites, fluid is taped and analysed using Xpert MTB/RIF Ultra® assay, liquid culture, and adenosine deaminase (ADA; Diazyme, Poway, USA). For liquid culture, bacteria growth indicator tube (MGIT), with a BACTEC 960 Instrument (BD Microbiology Systems, Sparks, MD) is used. In case of meningitis, lumbar puncture is performed and cerebrospinal fluid analysed with Xpert MTB/RIF Ultra® assay and liquid culture. In case of nuchal, cervical, or axillary lymphadenopathy, fine-needle aspiration biopsy (FNAB) is done for Ziehl-Neelsen stain, Giemsa- and Papanicolaou- stain for cytomorphology, and liquid culture. If liquid material is aspirated from a lymphnode, Xpert MTB/RIF Ultra® assay and culture is done. Patients with pericardial tamponade are referred for pericardiocentesis. Urine samples of 200 μl are frozen at − 80 °C in order to evaluate the novel lipoarabinomannan point of care test (FujiLAM) [20]. This will not affect the outcomes of this study.

In the intervention group, anti-tuberculosis treatment is started if any of the following is present: positive eFASH, chest x-ray with typical signs for tuberculosis, or positive microbiology from any site (Table 2). Anti-tuberculosis treatment is withheld and other causes than tuberculosis are considered if all microbiological tests are negative for *Mycobacterium tuberculosis*; eFASH does not show signs for extrapulmonary tuberculosis and no cavernous lesion, upper-lobe infiltrate or miliary pattern on the chest x-ray are seen. If the vena cava is dilated > 2 cm and collapsing less than 50% during inspiration and no eFASH signs are present, heart failure is considered. Presence of ascites with no other eFASH signs points at pelvic inflammatory disease (PID) in females, liver cirrhosis, nephrotic syndrome, heart failure, or at malignancy. Thickened ileum wall with loss of wall architecture and no other eFASH signs points at bacterial ileitis or Morbus Crohn. In case of ascites with otherwise negative eFASH, a full abdominal sonography to look for these diseases is done (Fig. 1).

**Table 2 Tab2:** Criteria for starting anti-tuberculous treatment in the intervention group

Positive eFASH	Multiple hypoechogenic lesions in the spleen or liver
	Pericardial effusion and no other clinical explanation
	Pleural effusion and no clinical or sonographic sign for heart failure (i.e normal V cava)
	Subpleural echogenic granular artefacts and B-lines
	abdominal, axillary, nuchal or cervical lymphnodes > 1.5 cm and no other clinical explanation for it
	Thickened ileum wall (> 4 mm) and loss of wall architecture and at least one another eFASH sign
	Ascites and at least one another eFASH sign
Chest X-ray with typical signs for tuberculosis	Cavernous lesion, upper-lobe infiltrate or miliary pattern
Positive microbiological result from any site	Positive Xpert MTB/RIF® assay and/or culture in sputum, pleural fluid, ascites, cerebrospinal fluid, or urine;
	Adenosine deaminase (ADA) ≥40 U/ml in pleural fluid, [21], ADA ≥ 35 U/ml in ascetic fluid [22], or ADA ≥35 U/ml in pericardial fluid [5];
	Positive fine needle aspiration result of lymph nodes (Xpert MTB/RIF® assay, culture, cytomorphology, identification of acid fast bacilli)

Patients allocated to the control group are diagnosed according to national guidelines [18] and the decision of the treating physician. Patients receive empirical treatment according to the discretion of the treating physician (Fig. 1). The treating physician of a control group patient is allowed to use ultrasound for puncturing pleural -or pericardial effusion, ascites, or lymph nodes, or in case of a serious acute problem during follow-up (e.g. suspected urolithiasis, cholecystitis, intestinal obstruction, perforation, appendicitis, or ruptured ectopic pregnancy). All patients who receive anti-TB treatment are routinely supervised by the treating Tuberculosis clinics of both sites by drug tablet return checking (weekly visits as per governmental guidelines, which can be also in a peripheral dispensary).

### Follow-up

In both groups, follow-up visits take place at two and 6 months after enrollment. Follow up visits include physical examination, and eFASH in the intervention group. If anti-tuberculosis treatment is not administered at enrollment, additional follow-up visits are done at two and 4 weeks. Transportation costs for study visits is paid by the study budget. If a patient misses an appointment, he or she will receive a phone call from the study team. If a patient is not reachable by phone, he or she is sought by an established collaboration with community health care workers or by physical tracking to the patients home by motorbike.

### Outcomes

The primary outcome is the proportion of correctly managed patients at 6 months. Secondary outcomes are the proportion of patients without symptoms at two and 6 months, and time to death. Other outcomes of interest are the proportions of patients with microbiologically-proven tuberculosis; with probable tuberculosis; with no tuberculosis; with a diagnosis other than tuberculosis; and receiving an invasive procedure. Safety outcomes are the occurrence of pneumothorax, major bleeding, and post-expansion pulmonary edema after interventions such as pleural tapping, ascites puncture or fine-needle aspiration.

### Definitions

A patient is defined as having definite tuberculosis if any of the microbiological tests is positive (Xpert TB/RIF®, Xpert Ultra TB/RIF®, culture, acid fast bacilli in fine-needle aspiration from lymphnodes, adenosine deaminase (ADA) ≥ 40 U/ml in pleural fluid [21], ADA ≥ 35 U/ml in ascetic fluid [22], or ADA ≥ 35 U/ml in pericardial fluid [5].

A patient is defined as having probable tuberculosis if all microbiological tests are negative, and clinical, radiological and sonographic (in the intervention group) signs improve, and body weight is stable or increases after 2 months of anti-tuberculosis treatment. A patient is defined not to have tuberculosis if all microbiological tests were negative, and (a) clinical signs, symptoms and radiological signs (and in patients in the intervention group sonographic signs) improved, and body weight increased, without start of anti-tuberculosis treatment or (b) a diagnosis other than tuberculosis was found explaining the symptoms in a patient with or without anti-tuberculosis treatment.

A correctly managed patient is defined as one who had definite or probable tuberculosis and was treated with anti-tuberculosis treatment; or a patient who did not have tuberculosis and was not treated with anti-tuberculosis treatment.

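### The primary outcome is scored by different rules in the two arms: probable tuberculosis needs sonographic improvement in the intervention arm only

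*Protocol article*

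**What the plan says.** The Outcomes section states: "The primary outcome is the proportion of correctly managed patients at 6 months". The Definitions section makes this depend on each patient's tuberculosis class: "A correctly managed patient is defined as one who had definite or probable tuberculosis and was treated with anti-tuberculosis treatment", or as one without tuberculosis who was not treated. The classes are:

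- **Definite tuberculosis:** any positive microbiological test, including adenosine deaminase above a cut-off. No improvement is required.
- **Probable tuberculosis:** negative microbiology, "clinical, radiological and sonographic (in the intervention group) signs improve", and stable or rising weight after 2 months of treatment.
- **No tuberculosis, route (a):** negative microbiology, no treatment started, and "clinical signs, symptoms and radiological signs (and in patients in the intervention group sonographic signs) improved, and body weight increased".
- **No tuberculosis, route (b):** negative microbiology and "a diagnosis other than tuberculosis was found explaining the symptoms in a patient with or without anti-tuberculosis treatment". No improvement is required.

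The Follow-up section matches the arm-specific wording: "Follow up visits include physical examination, and eFASH in the intervention group". Protocol eFASH is not done in the control arm.

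**The concern.** The conditions for probable tuberculosis and for route (a) are joined by *and*. An added condition can move patients out of a class but never into it, and here it is added in one arm only. Two patients with the same disease, treatment and clinical and radiological recovery can therefore be scored differently because of allocation alone. Randomisation balances the patients; it cannot balance a difference written into the outcome rule. The estimated odds ratio would then mix the effect of the management algorithm with the effect of a stricter definition in the arm that receives it.

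**Working it through.** **1. Which patients the rule affects.** The class definitions are set against the treatment criteria (Study procedures section and Table 2).

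| Route | Sonographic condition in intervention arm | Practical effect |
|---|---|---|
| Definite tuberculosis | none | none |
| Probable tuberculosis | yes | affects treated, microbiology-negative patients with eFASH signs |
| No tuberculosis (a) | yes | small: the algorithm withholds treatment only when eFASH shows no signs of extrapulmonary tuberculosis, so there is usually nothing to improve |
| No tuberculosis (b) | none | none |

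The affected group is mainly the treated, microbiology-negative, eFASH-positive patients. A positive eFASH is by itself a criterion for starting treatment in this arm, so the algorithm creates such patients.

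**2. One patient followed through both arms.** Microbiology is negative and treatment is given. At 2 months clinical and radiological signs have improved and weight is stable, but an enlarged node or effusion has not improved on ultrasound.

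- *Intervention:* not definite; not probable, because the sonographic condition fails; not route (a), because treatment was started; route (b) only if another diagnosis is found. Otherwise the patient fits no class and does not meet the definition of correctly managed.
- *Control:* the sonographic condition does not exist. The patient is probable tuberculosis, treated, and correctly managed.

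**3. The plan's own sample size.** Inputs (Sample size section): 73% control, 85% intervention, power 95%, two-sided alpha 0.05, 592 patients before loss to follow-up; 1:1 allocation (Randomization section). With pooled variance,

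n per arm = [(1.960·s0 + 1.645·s1)/d]², where s0 = √(2·p̄(1−p̄)) and s1 = √(p1(1−p1) + p2(1−p2)).

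Here p̄ = 0.79, s0 = 0.5760, s1 = 0.5697 and d = 0.12, so n = 296.4, rounded up to 297 per arm or 594 in total. The stated 592 is reproduced within rounding.

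**4. Power if the extra condition lowers the intervention proportion.** The documents give no failure rate, so this is an assumed range: 10–20% of intervention patients are treated, microbiology-negative and eFASH-positive, and 5–15% of those meet the other conditions but do not improve sonographically.

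- Low end: 0.10 × 0.05 = 0.005, or 0.5 points.
- High end: 0.20 × 0.15 = 0.03, or 3 points.

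Power = Φ[(d·√n − 1.960·s0)/s1] with n = 296 per arm and control at 73%:

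| Loss (points) | Intervention | d | z | Power |
|---|---|---|---|---|
| 0 | 85.0% | 0.120 | 1.642 | 95.0% |
| 0.5 | 84.5% | 0.115 | 1.475 | 93.0% |
| 1 | 84.0% | 0.110 | 1.309 | 90.5% |
| 2 | 83.0% | 0.100 | 0.984 | 83.7% |
| 3 | 82.0% | 0.090 | 0.666 | 74.7% |

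The table counts a patient in no class as not correctly managed, as the definition reads. If such patients were instead excluded, a 3-point loss would give 0.82/0.97 = 84.5%, a fall of about half a point in the proportion. The direction is the same and the size smaller.

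**The case against.** Several points on the other side stand.

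- **Radiology.** A reader might infer that the radiological criterion adds to the imbalance, or that it cannot be scored because no repeat chest X-ray is listed at follow-up. The documents do not support either. Radiological improvement is required in both arms. The Follow-up section says what visits include, which is not an exhaustive list, and the full protocol and Table S1 are not shown.
- **Size.** A reader might count every patient with residual sonographic signs as a failure and arrive at a large loss of power. The text asks that signs improve, not that they resolve. A smaller but still visible node or effusion passes. Patients treated on X-ray alone, with no eFASH sign, have nothing sonographic to improve. The 85% rests on Table S2, which is not shown, so it may already allow for some of this.
- **Net direction.** A reader might infer that the trial as a whole is biased against the intervention. That is not established. The intervention algorithm adds a full abdominal sonography for isolated ascites, which can find other diagnoses and so place untreated patients in route (b).
- **Value of the information.** Sonographic response is real information, and the examinations are reviewed by an independent sonographer. A classification without it leans more on clinical items judged open-label.
- **Timing.** The Timeline section reports 538 patients already included of the planned 650, so changing a primary definition is more than an edit of wording.

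These points limit the size and the claimed direction. None of them gives the two arms the same rule. Nor is this detail that an article leaves to a fuller document: the article states the definition, and states it differently by arm.

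**Conclusion.** The point holds in a limited form. The primary outcome is defined differently by arm through the sonographic condition for probable tuberculosis and, to a minor extent, route (a). It acts mainly on treated, microbiology-negative, eFASH-positive intervention patients who recover clinically without sonographic improvement by 2 months. Considered alone it can only lower the intervention proportion; the sign of the overall bias is unknown. Under the assumed loss of 0.5 to 3 points, power falls from 95% to between 93% and 75%. That range rests on assumed shares, on the planned 85% and 73% describing a common rule, and on unclassified patients counting as not correctly managed. The sample size calculation itself is sound. The lack of a common rule is certain from the text; its numerical effect is not.

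**What to change.** Before any outcome is tabulated by arm, define probable tuberculosis and no tuberculosis for the primary analysis by one rule in both arms. Use items assessed identically: symptoms, physical examination and body weight. Include radiology only if the repeat film is scheduled the same way in both arms; counting it wherever a film happens to exist could itself differ by arm in an open-label trial. Leave the sonographic condition out of the primary classification. Keep the present sonography-inclusive definition as a prespecified sensitivity analysis, and report how many intervention patients change class between the two.

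The cost is a documented change to the primary outcome definition, recorded with its date and reason, and one further analysis. No new data are needed. The downside is that some imaging information available in the intervention arm is not used in the primary classification. The article says that no interim analysis requiring a data monitoring committee is planned and that a full analysis plan is still to be developed, so that plan is the natural place for the change.

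### Probable tuberculosis and route (b) of 'no tuberculosis' are not mutually exclusive, so one kind of treated patient has two labels with opposite implications for the primary outcome

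*Protocol article*

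**What the plan says.** All the relevant rules are in the Definitions section of the protocol article.

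- **Probable tuberculosis.** The definition opens "A patient is defined as having probable tuberculosis if all microbiological tests are negative" and then requires that "clinical, radiological and sonographic (in the intervention group) signs improve, and body weight is stable or increases after 2 months of anti-tuberculosis treatment". It has no condition about other diagnoses.
- **No tuberculosis.** All microbiology must be negative, and one of two routes must apply. Route (a) is improvement "and body weight increased, without start of anti-tuberculosis treatment". Route (b) reads "b) a diagnosis other than tuberculosis was found explaining the symptoms in a patient with or without anti-tuberculosis treatment". Route (b) sets no condition on clinical course and does not exclude patients who improved on treatment.
- **Correctly managed.** There are two limbs, joined by 'or'. The first is "one who had definite or probable tuberculosis and was treated with anti-tuberculosis treatment". The second covers untreated patients classed as free of the disease.

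The Outcomes section then states: "The primary outcome is the proportion of correctly managed patients at 6 months". It lists the proportions with probable tuberculosis and with no tuberculosis as separate further outcomes. The article gives no order of precedence and no adjudication rule for a patient who meets two definitions.

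**The concern.** The two definitions describe overlapping groups. Consider a microbiology-negative patient who starts anti-tuberculosis treatment, is then found to have another condition that explains the symptoms, and is better with stable weight at two months. This patient satisfies probable tuberculosis and also satisfies route (b). The first label puts the patient in the first limb of correct management. The second label describes someone treated without having the disease, whom the second limb does not count as correctly managed.

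This matters because the Discussion and conclusion give reduced overtreatment as the trial's purpose, and a treated patient whose symptoms have another explanation is a candidate case of overtreatment. The trial is open-label, and Data collection and management says the study group can see the clinical, microbiological and sonographic findings. If the article's rules are all there is, someone has to decide which label applies while knowing the arm.

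**Working it through.** **1. The plan's own figure.** Inputs from Sample size: 73% against 85% correctly managed, two-sided alpha 0.05, power 95%. The standard formula for two proportions with pooled variance is

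n per arm = [z(α/2)·√(2p̄q̄) + z(β)·√(p₁q₁ + p₂q₂)]² / (p₂ − p₁)²

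With p̄ = 0.79, this is [1.960·√0.3318 + 1.645·√0.3246]² / 0.12² = 296.5. That rounds to 297 per arm, or 594 in all, against 592 stated. The figure reproduces, and this point does not change it.

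**2. Where the definitions overlap.** Five features decide the class: microbiology (positive or negative), treatment (yes or no), signs improved (yes or no), weight (up, stable or down) and another explanatory diagnosis (yes or no). That gives 2 × 2 × 2 × 3 × 2 = 48 combinations. Exactly two are both tuberculosis and no tuberculosis:

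| Microbiology | Treated | Signs improved | Weight | Other diagnosis | Probable TB | No TB, route (b) |
|---|---|---|---|---|---|---|
| negative | yes | yes | up | yes | met | met |
| negative | yes | yes | stable | yes | met | met |

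Route (a) cannot overlap with probable tuberculosis because it requires that treatment was not started. Definite tuberculosis cannot overlap with either route because both need negative microbiology.

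**3. What the overlap can do to the comparison.** Let q_C and q_I be the shares of the control and intervention arms in these two rows. Suppose the planning rates count such patients as correctly managed; the article does not say whether they do. Giving route (b) precedence then changes the difference from 12 points to 12 − (q_I − q_C) points. The shares below are assumptions. Power is at 296 per arm, by the inverse of the formula above.

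| q_C | q_I | Control vs intervention | Difference | Power |
|---|---|---|---|---|
| 0% | 0% | 73% vs 85% | 12 | 0.950 |
| 2% | 2% | 71% vs 83% | 12 | 0.936 |
| 5% | 5% | 68% vs 80% | 12 | 0.916 |
| 0% | 5% | 73% vs 80% | 7 | 0.519 |
| 5% | 0% | 68% vs 85% | 17 | 0.999 |

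For scale, 5% of 296 is about 15 patients. Equal shares cost a little power and leave the difference alone. Only unequal shares move the difference, and they can move it either way.

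**4. Whether shares could differ by arm.** The text gives two reasons why they might. Probable tuberculosis requires sonographic improvement in the intervention arm only. The intervention algorithm also directs a search for other causes, such as heart failure by vena cava assessment, and full abdominal sonography when ascites is the only finding, whereas control patients follow national guidelines and the treating physician. The article gives no data on the net effect.

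**The case against.** The strongest reply is that nothing is contradictory in the scoring. The article defines only correct management, as two limbs joined by 'or'. The overlap patient meets the first limb and so counts as correct; an incorrectly managed category is not defined at all. This stands as far as it goes: a reader might infer that the same patient is scored both correct and incorrect, and the text does not say that. But the literal reading counts as correctly managed a treated patient whom the same section defines as not having tuberculosis. It also puts that patient in two proportions that Outcomes lists separately.

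A second reply is that a diagnosis which explains the symptoms already rules tuberculosis out. If that is the intention, route (b) should take precedence, but the definition of probable tuberculosis does not say so.

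A third is that the statistical analysis plan, announced but not shown, may set the order. It may, so case-by-case choice cannot be asserted as fact. The conflict is nevertheless between two rules that the article states in full, not a detail it leaves open.

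A fourth is that putting route (b) first ties the primary outcome to how hard other diagnoses are sought, which favours neither arm by design but differs between them. This also stands, and the fix has to allow for it.

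**Conclusion.** The overlap is real and sits in the definition of the primary outcome. It is confined to treated, microbiology-negative patients whose signs improve with stable or rising weight and who have another explanatory diagnosis. For them the two labels imply opposite management status, and the article gives no rule for choosing.

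The share of such patients, and the size and direction of any between-arm bias, cannot be computed from the documents; the table above illustrates assumed shares only. Two stronger inferences are not supported. One is that overtreatment would be largely hidden: treated patients with another diagnosis who do not meet the improvement or weight criteria remain in route (b), and no figure shows which group is larger. The other is that a shift in one arm's proportion can be read against the planned 12 points: equal shifts cancel, and only the difference between the arms' shares counts.

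**What to change.** Before outcomes are classified, make the classes mutually exclusive by a documented amendment. One way is to add to probable tuberculosis the condition that no other diagnosis accounting for the symptoms has been made. This agrees with route (b), which expressly covers treated patients. Apply the same order to every patient in both arms, with classification blind to arm where existing staff allow. Report a sensitivity analysis in which probable tuberculosis takes precedence, and give the number of overlap patients in each arm alongside it.

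The cost is one sentence in the definition, the amendment itself and one extra analysis; treatment and visits do not change. The Timeline records 538 of 650 patients included by 30 March 2020, so the date and reason for the change should be recorded. The downsides are that the proportion correctly managed may fall in both arms, and that the primary result may depend on how actively other diagnoses are looked for, which the intervention algorithm does more. The sensitivity analysis shows how far the result depends on that choice.
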